## Abstract

**Background:**

Ulcerative colitis (UC) is a chronic non-specific inflammatory intestinal disease, categoried under "dysentery" and "intestinal bleeding" in Traditional Chinese Medicine (TCM). Jianpi Qingchang decoction (JPQC) is a combination formula specifically designed for the treatment of UC. The primary objective of this study is to examine the clinical efficacy of JPQC in individuals diagnosed with UC who exhibit both spleen deficiency and dampness-heat syndrome, along with the presence of fatigue. The investigation will focus on assessing the impact of JPQC on the gut microbiota and metabolites in these patients, aiming to elucidate the regulatory mechanism that JPQC exerts on the gut microbiota and metabolites in the context of UC-related fatigue.

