**Discussion:**

If effective, JPQC will provide substantial clinical evidence concerning the effectiveness and safety in the treatment of patients with UC experiencing spleen deficiency and dampness-heat syndrome accompanied by fatigue.

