## Introduction

1

Ulcerative colitis (UC) is a chronic, non-specific inflammatory intestinal disease primarily affecting the colorectal mucosa and submucosa, categorized under inflammatory bowel disease (IBD). It is estimated that the global prevalence of ulcerative colitis will reach 5 million cases in 2023, with a rising incidence worldwide [1]. The main clinical symptoms of UC include persistent or frequent episodes of diarrhea and mucous purulent and bloody stools. These symptoms may be accompanied by systemic manifestations such as abdominal pain, acute diarrhea, and fatigue.

Fatigue, characterized by a disproportionate lack of energy or exhaustion to physical exertion, adversely affects daily activities and cannot be alleviated by rest [2]. It is a multifaceted, multifactorial symptom associated with various chronic diseases [3]. Notably, Fatigue is a significant clinical symptom for patients with IBD [4], reaching a prevalence of 86 % in those with active IBD and 50 %–52 % in those with mild to inactive IBD [5]. In Chinese patients with UC, the prevalence rate of fatigue is 61.8 %, with higher rates in active disease (68.2 %) than in remission (40.0 %). Factors such as Montreal classification, disease activity, and anxiety are linked to an increased risk of fatigue risk Background [6]. The presence of fatigue in patients with UC is associated with a diminished quality of life [7]. Addressing fatigue is crucial not only for improving the care and quality of life for patients with UC but also for reducing direct medical expenses and the indirect economic impact on work productivity and function [8]. Therefore, it is particularly important to find practical and effective ways to intervene fatigue for improving the care and quality of life of patients with UC.

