Traditional Chinese medicine (TCM) posits that the weakness of the spleen and stomach, exogenous pathogens, improper diet, and emotional disorders can contribute to UC. The disease primarily affects the large intestine and is characterized by spleen deficiency, and dampness-heat, blood stasis, and phlegm-dampness. UC is further categorized into seven syndrome types, such as spleen deficiency and dampness accumulation syndrome, large intestine damp-heat syndrome, excessive heat toxin syndrome and liver depression and spleen deficiency syndrome, with spleen deficiency and dampness accumulation syndrome and large intestine damp-heat syndrome being common [9]. In our previous study, we observed varying degrees of fatigue symptoms in patients with damp-heat syndrome of the large intestine and spleen deficiency and dampness accumulation syndrome. Fatigue was notably more prevalent and severe in the latter. Patients with UC and damp-heat syndrome of the large intestine exhibited symptoms such as "stagnation of wetness-evil," characterized by a heavy head, heavy body sleepiness, and sore limbs, among which heavy body sleepiness is its representative symptom. In contrast, patients with UC with spleen deficiency and dampness accumulation syndrome manifested "weakness" symptoms, including listlessness, fatigue, and weakness of limbs, among which fatigue and weakness are its characteristic symptoms. This finding holds significant guidance for clinical syndrome differentiation and the treatment of UC-related fatigue. The methods involving clearing heat and eliminating dampness, invigorating the spleen, and benefiting qi, as explored in this study, offer valuable insights into therapeutic approaches for managing UC-related fatigue [10]. Guided by the principles of invigorating the spleen and qi, clearing away heat and toxic materials, cooling blood and stopping bleeding, and regulating qi and relieving pain, we formulated and optimized Jianpi Qingchang decoction (JPQC) consisting of *Astragalus membranaceus (Huang Qi)30**g, Portulaca oleracea (Ma Chi Xian)30g, Codonopsis pilosula (Dang Shen)15g, Coptidis Rhizoma (Huang Lian)3 g, Sanguisorba officinalis (Sheng Di Yu)15g, Panax notoginseng (San Qi)6g, Bletilla striata (Bai Ji)3g, Radix Aucklandiae (Mu Xiang)6g, and Radix Glycyrrhizae (Sheng Gan Cao)6g* [11]. Forty-four phytochemicals, including astragaloside A, oleracein A, and coptisine, were identified from JPQC using the ultra-high performance liquid chromatography-quadrupole time-of-flight mass spectrometry (UPLC-Q-TOF/MS) method [12]. Our previous study revealed that JPQC effectively alleviated clinical symptoms of abdominal pain and diarrhea in patients with mild-moderate UC, improved mental fatigue, and increased quality of life [13,14]. However, there is a limited exploration of the impact of JPQC on fatigue in patients with UC with spleen deficiency and dampness-heat syndrome. Consequently, we have designed a randomized controlled clinical trial to comprehensively investigate the effectiveness and safety of JPQC in treating patients with UC with spleen deficiency and dampness-heat syndrome accompanied by fatigue. This research aims to contribute valuable insights into potential therapeutic interventions for addressing fatigue in patients with UC, particularly those with spleen deficiency and dampness-heat syndrome.

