**Fig. 1 fig1:**
[figure not shown]
The flow chart of the trial.

This is a randomized controlled multicenter clinical trial comprising two parallel groups. From January 2024 to June 2025, 140 patients meeting the diagnostic criteria and syndrome types of UC will be recruited. During the recruitment process, potential participants meeting the inclusion criteria will be thoroughly informed about the study's purpose, examinations, intervention measures, and follow-up procedures. Upon obtaining informed consent, eligible subjects will be randomly assigned to two groups in a 1:1 ratio. The groups will receive either JPQC combined with mesalazine or mesalazine intervention for 12 weeks. The UC patients will be followed up again after 6 months. The schedule details are listed in Table 1.

**Table 1 tbl1:** Schedule of trial.

Period	enrollment	baseline	treatment			follow-up
time points	week-1	week 0	week 4	week 8	week 12	week 24
patients						
Informed consent	✓					
Inclusion/Exclusion criteria	✓					
Medical history	✓					
Physical examination	✓					✓
Laboratory examination	✓					✓
Randomization	✓					
Intervention						
Jianpi Qingchang decoction(JPQC) group	JPQC:two times daily; + mesalazine: 1g/three times daily					
Mesalazine control group	1g/three times daily					
Outcomes						
Inflammatory bowel disease fatigue scale(IBD-F)		✓	✓	✓	✓	✓
Inflammatory Bowel Disease Questionnaire (IBDQ)		✓	✓	✓	✓	✓
TCM symptom efficacy		✓	✓	✓	✓	✓
Modified Mayo score		✓			✓	✓
Simple clinical colitis activity index (SCCAI)		✓				
Intestinal microbial diversity and non-targeted metabonomics		✓			✓	
Trial evaluation						
Safety of medicine		✓	✓	✓	✓	✓
Adverse event		✓	✓	✓	✓	✓
Reasons of drop-outs or withdrawals		✓	✓	✓	✓	
Patient's compliance					✓	

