#### Inclusion criteria

2.2.2

1)Age between 18 and 70 years old, both male and female.2)Diagnosis of ulcerative colitis confirmed by electronic colonoscopy and pathology, meeting the criteria established by the consensus on the diagnosis and treatment of inflammatory bowel disease (2018 Beijing) [15].3)Adherence to the 2018 Guidelines for Diagnosis and Treatment of Ulcerative Colitis, a Common Disease of Digestive System [16], TCM Syndrome Differentiation Criteria for spleen deficiency and dampness-heat syndrome.4)Underwent enteroscopy within the past 1 year.5)Absence of serious heart, liver, kidney, and other significant organ and blood system diseases.6)Full understanding of the purpose and content of the test, good compliance, and voluntary signing of the informed consent form.

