#### Primary outcome

2.4.1

The primary outcome of the study is the inflammatory bowel disease fatigue scale(IBD-F), which will be measured at baseline and 4, 8, 12 weeks after randomization. The IBD-F consists of 3 parts. Possible scores are 0–20 and 0–120 in part I and II, respectively. If the ‘not applicable – N/A’ (not applicable) option is checked (questions 3, 4, 9, 12, 13, 14), a corrected result has to be calculated from the following formula: Corrected result = actual total result/(120 – number of N/As × 4) × 120 [19].

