##### TCM symptom efficacy

2.4.2.2

TCM symptom efficacy evaluation criteria will refer to the TCM Symptom Score Table for Gastrointestinal Diseases [21]. The scores of 0, 3, 5, and 7 represented no symptoms, mild, moderate, and severe symptoms, respectively, where the main symptoms included abdominal pain, diarrhea,mucous purulent bloody stool, tenesmus, anal burning, and the secondary symptoms included dry mouth with bitter taste in mouth, poor food intake and poor appetite, fatigue, lazy word.

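### Fatigue defines the target population and the primary outcome, but no entry criterion states it, and the fatigue scale is scheduled too late to screen for it

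*Protocol article*

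**What the plan says.** **Target population.** The Abstract (Background) sets the objective in individuals with UC "who exhibit both spleen deficiency and dampness-heat syndrome, along with the presence of fatigue". Section 1 gives the aim as "treating patients with UC with spleen deficiency and dampness-heat syndrome accompanied by fatigue". The Abstract (Discussion) frames the conclusion for "patients with UC experiencing spleen deficiency and dampness-heat syndrome accompanied by fatigue", and section 3 repeats this population.

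**Primary outcome.** Section 2.4.1 names IBD-F, scored 0–20 in part I and 0–120 in part II.

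**Who may enter.** Section 2.1 states that "140 patients meeting the diagnostic criteria and syndrome types of UC will be recruited". Section 2.2.2 lists six criteria: age, confirmed UC, the syndrome, enteroscopy within a year, no serious organ or blood disease, and understanding, compliance and consent. The syndrome criterion refers to "TCM Syndrome Differentiation Criteria for spleen deficiency and dampness-heat syndrome" in a cited guideline. Section 2.2.3 lists nine exclusions, none of which concerns absence of fatigue. No disease-activity criterion is set.

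**Timing.** Table 1 places the eligibility check and randomisation at week -1 and the first IBD-F at week 0.

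**How common fatigue is.** Section 1 says: "In Chinese patients with UC, the prevalence rate of fatigue is" 61.8%, with 68.2% in active disease and 40.0% in remission.

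**The concern.** The sections that say whom the trial is about and the section that says who may enter do not match. The objective treats fatigue as something present in addition to the syndrome; the entry list asks only for the diagnosis and the syndrome.

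Two things are at stake. A patient who scores low on IBD-F at the start has little room to improve, so such patients shrink the between-group difference on the primary outcome. And a result from a mixed group would describe UC with this syndrome, not the fatigued patients named in the conclusion.

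**Working it through.** **Step 1: look for a fatigue requirement in the text.**

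| Place | Is fatigue a condition of entry? |
|---|---|
| Abstract, section 1, section 3 (aims and conclusion) | Fatigue defines the population |
| Section 2.1 (recruitment) | No; diagnosis and syndrome type only |
| Section 2.2.2 (six inclusion criteria) | Not stated; the syndrome criterion defers to a guideline not shown |
| Section 2.2.3 (nine exclusion criteria) | No |
| Table 1 | IBD-F first at week 0; eligibility and randomisation at week -1 |

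As scheduled, IBD-F cannot serve as a screen, and no criterion refers to it.

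**Step 2: the plan's sample size.** Section 2.2.6 uses effective rates of 71% and 94.12%. Mean p = 0.8256, q = 0.1744, difference = 0.2312. The printed formula gives:

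- one-sided 0.05, 90% power: 2 × 0.8256 × 0.1744 × (1.645 + 1.282)² / 0.2312² = 46.1, so 47 per group;
- two-sided 0.05, 90% power: the same with 1.960 in place of 1.645 = 56.6, close to the printed 56.

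The printed 56 therefore fits a two-sided test, although the text says unilateral. Then 56 / (1 − 0.20) = 70 per group, 140 in total, as stated. The calculation is for an effective rate, so the protocol makes no power statement for IBD-F.

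**Step 3: hypothetical dilution.** Assumptions, none of them from the protocol: 56 evaluable per group; a standardised effect d among fatigued patients giving 90% power at two-sided 0.05; no effect in the others; equal SD.

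- d = (1.960 + 1.282) × √(2/56) = 0.613.
- With a fatigued share f the average effect is f × d, and power = Φ(f × 3.242 − 1.960), where 3.242 = 1.960 + 1.282.
- Example, f = 0.618: 0.618 × 3.242 = 2.003; 2.003 − 1.960 = 0.043; Φ(0.043) = 0.52.
- One-sided at 0.05, rescaled to 90% power: Φ(f × 2.926 − 1.645).
- Screening needed for 140 = 140 / f.

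| Fatigued share f | Source | Power, two-sided | Power, one-sided | Screened for 140 |
|---|---|---|---|---|
| 40.0% | section 1, remission | 25% | 32% | 350 |
| 61.8% | section 1, all UC | 52% | 57% | 227 |
| 68.2% | section 1, active UC | 60% | 64% | 206 |
| 80% | assumed | 74% | 76% | 175 |
| 86% | assumed | 80% | 81% | 163 |

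At the three general-UC rates, about 84, 53 or 45 of 140 patients would have no fatigue (140 × (1 − f)).

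**The case against.** **The syndrome may already bring in fatigue.** This is the strongest argument. The syndrome criterion imports a guideline that cannot be checked here. Section 1 also presents fatigue and weakness as characteristic of a related syndrome, spleen deficiency with dampness accumulation. A reader might infer from the entry list that patients without fatigue will certainly be enrolled; the documents do not establish that. Nor do they say that the syndrome requires fatigue. Section 1 reports varying degrees of fatigue across two related syndromes, and the aims add fatigue to the syndrome. Section 2.4.2.2 lists it among secondary symptoms ("poor food intake and poor appetite, fatigue, lazy word"), where 0 means absent. That table scores an outcome and rests on a different reference, so it is weak evidence about entry. Even if the guideline requires fatigue, the article sets no IBD-F level.

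**An article condenses.** True, but both lists are printed as numbered lists, down to legal capacity, and the missing item is the one that defines the population.

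**The timing is not fully clear.** Section 2.4.1 counts weeks from randomisation, which could put randomisation at week 0. Fatigue could also be judged clinically. Both points stand, but no criterion asks for either.

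**The power figures are not estimates for this trial.** This stands. A reader might infer that the trial has only 52% power. The protocol never claims 90% power on IBD-F. The prevalence figures are for UC in general, and the share within this syndrome is not given and may be higher. Zero effect in the remainder is a worst case, and being classed as not fatigued does not mean an IBD-F score of zero.

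**Conclusion.** The mismatch between the stated population and the entry criteria is established by the text and needs no arithmetic. That patients with little or no fatigue can enter is conditional: it holds unless the cited syndrome guideline requires fatigue, which the article does not say.

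The direction of the consequence, a smaller difference on IBD-F and a result that does not match the conclusion, follows from mixing such patients in. Its size cannot be derived from the documents. The 25% to 80% range is an illustration that rests on an assumed effect size, no effect in non-fatigued patients, equal SD and a fatigued share between 40% and 86%. Using the stated one-sided level changes it to 32% to 81%, with the same direction.

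**What to change.** 1. Move the baseline IBD-F to the week -1 visit, before randomisation, and correct Table 1.
2. Add an explicit inclusion criterion requiring fatigue, with a pre-stated IBD-F threshold. The sponsor must set it; the documents offer no basis for a value. If the cited guideline already requires fatigue, say so in section 2.2.2 as well.
3. For patients already randomised, keep all of them in the primary analysis, adjust for baseline IBD-F, and report those meeting the threshold as a supportive analysis. Fix the threshold before outcome data are seen. That subset should not become primary: on the printed schedule their IBD-F was completed after randomisation, and the control group receives mesalazine alone, so allocation could influence the self-report that selects them. Adjustment removes no randomised patient.

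The cost is an amendment, one questionnaire given earlier, and more screening. If 61.8% are fatigued, about 227 otherwise eligible patients are needed to reach 140; at 40.0% it is 350, at 86% about 163. Over the 18 months from January 2024 to June 2025, 227 means about 12.6 patients screened per month instead of 7.8, so recruitment may need longer.

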#### Exclusion criteria

2.2.3

1)Participation in other clinical trials in the past 6 months.2)Use of antibiotics in the last 3 months.3)Use of immunosuppressants, biological agents, other non-steroidal (steroidal) anti-inflammatory drugs, gastrointestinal mucosal protective agents, intestinal probiotics and probiotics in the past 4 weeks.4)Pregnant or lactating women.5)Presence of gastric and duodenal ulcers, history of intestinal surgery, intestinal obstruction, intestinal perforation, perianal abscess, severe hemorrhagic disease, or tumor.6)Patients with mental illness, are unable to control themselves, or lack autonomy.7)Lack of legal capacity or limited legal capacity.8)History of other diseases estimated by researchers to interfere with trial results or increase patient risk.9)Any other circumstances deemed unsuitable for participating in the study by the researcher.

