#### Sample sizes

2.2.6

Based on the literature findigns, the control group treated with mesalazine showed a 12-week effective rate of 71 % [17], while the experimental group treated with JPQC recipe and mesalazine exhibited an effective rate of 94.12 % in 12 weeks [18]. Considering a clinical difference to improve the effective rate, with α set at a unilateral level of 0.05 and β at 0.10, the sample size calculation was performed using the formula$$n=\frac{{2\bar{p}\bar{q}\left(Z_{\alpha }+Z_{\beta }\right)}^{2}}{{\left(p1-p2\right)}^{2}}$$

This yielded a sample size of approximately 56 cases for each group (n1 = n2 ≈ 56 cases). Accounting for a dropout rate of 20 %, the study required a total of 140 cases, with 70 patients in the control group and 70 patients in the test group.

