#### The control group

2.3.2

The control group receiving mesalazine alone.

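### Both arms receive mesalazine, but entry criteria are silent on prior mesalazine use and the stated t-test ignores it, so the IBD-F effect averages two different contrasts

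*Protocol article*

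**What the plan says.** **Treatment.** Section 2.1 of the protocol article states: "The groups will receive either JPQC combined with mesalazine or mesalazine intervention for 12 weeks". Section 2.3.2 describes the comparator in one line: "The control group receiving mesalazine alone".

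**Eligibility.** Exclusion 3 (section 2.2.3) bars "Use of immunosuppressants, biological agents, other non-steroidal (steroidal) anti-inflammatory drugs, gastrointestinal mucosal protective agents, intestinal probiotics and probiotics in the past 4 weeks", and exclusion 2 bars antibiotics in the last 3 months. Mesalazine is not named, and the word for further anti-inflammatory drugs in exclusion 3 can be read as exempting it. The inclusion criteria (section 2.2.2) cover age, diagnosis, TCM syndrome, endoscopy, organ disease and consent. None concerns prior or current mesalazine, and none sets a level of disease activity.

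**Allocation and analysis.** Section 2.1 says "eligible subjects will be randomly assigned to two groups in a 1:1 ratio" and names no stratification factor. Section 2.7 names two-sample t-tests for means, with nonparametric alternatives. Table 1 places a medical history at week -1, in the same column as randomisation.

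**Outcomes and planning.** The primary outcome is the IBD-F score (section 2.4.1). Stool microbiota and metabolites are measured before and after treatment (section 2.5). The sample size assumes that "the control group treated with mesalazine showed a 12-week effective rate of 71" per cent, from a cited source whose patients are not described.

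**The concern.** For a patient who starts mesalazine at week 0, the trial compares JPQC plus a newly started drug with that drug. For a patient already taking it, the trial compares JPQC added to continuing treatment with continuing treatment, and the control arm may bring nothing new. These are different questions, and the expected 12-week change in IBD-F need not be the same in both.

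The stool outcomes have the same difficulty. Baseline stool is guarded against recent antibiotics and probiotics, but it can be a pre-mesalazine sample in one patient and an on-mesalazine sample in the next. Section 3 gives the effect on intestinal flora and metabolites as the study's main aim and describes JPQC combined with mesalazine as acting on them, so this affects a comparison the investigators care about.

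At stake are the interpretation of the pooled effect, some precision, and protection against chance imbalance.

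**Working it through.** **1. The plan's own figure.** Section 2.2.6 uses n = 2·p̄·q̄·(Zα+Zβ)²/(p1-p2)² with rates 0.71 and 0.9412, so p̄ = 0.8256 and q̄ = 0.1744.
- One-sided α = 0.05, β = 0.10, as stated: n = 46.1, i.e. 47 per group.
- Two-sided α = 0.05: n = 56.6, which matches the stated 56.
- Dropout: 56/(1-0.20) = 70 per group, 140 in total. This reproduces.

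The sidedness mismatch is a separate matter and this point does not depend on it. The figures carried forward are 70 randomised and 56 evaluable per arm.

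**2. Who can enter.** Setting sections 2.2.2 and 2.2.3 beside 2.3, no written criterion excludes a new starter and none clearly excludes a current user. Both can enter. The share of each is not given, so prevalence f is assumed to be 30-70%.

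**3. Chance imbalance in prior use, 70 per arm.** 95% limit = 1.96·√(2f(1-f)/70).
- f = 0.3 or 0.7: 1.96·√0.0060 = 15.2 points.
- f = 0.5: 1.96·√0.00714 = 16.6 points.
- At f = 0.5 one standard deviation is 8.5 points, and the probability of a gap above 10 points is about 24%.

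**4. Effect on IBD-F.** Assume prior use shifts week 12 IBD-F by d = 0.3, 0.5 or 0.8 within-group SD, with f = 0.5. Share of variance removed by adjustment = f(1-f)d²/(1+f(1-f)d²).
- d = 0.3: 0.0225/1.0225 = 2.2%.
- d = 0.5: 0.0625/1.0625 = 5.9%.
- d = 0.8: 0.16/1.16 = 13.8%.

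An imbalance at the 16.6-point limit would move the unadjusted difference by 0.166 × 0.3 = 0.05 SD up to 0.166 × 0.8 = 0.13 SD.

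**5. What stratum results could show.** With 56 evaluable per arm and f = 0.5, each stratum has 28 per arm, and the 95% half-width for a difference is 1.96·√(2/28) = 0.52 SD. At f = 0.3 the smaller stratum has about 17 per arm (56 × 0.3 = 16.8) and a half-width of 1.96·√(2/17) = 0.67 SD. For the whole trial it is 1.96·√(2/56) = 0.37 SD.

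**6. Stool.** Among non-users, change from baseline to week 12 contains the start of mesalazine. Among users it does not. The randomised contrast between arms shares this mix in expectation. A within-arm before/after reading does not separate the two.

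**The case against.** Most of the case on the other side stands. Randomisation balances prior use in expectation, and the unadjusted test keeps its type I error because chance imbalance is already in its standard error. A mixed population on a standard comparator is an ordinary pragmatic design. The article is condensed, so stratification factors and covariates may sit in a full protocol or SAP that is not shown, and their absence here proves nothing. Exclusions 8 and 9 leave investigators discretion over entry.

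A reader might go further and infer that patients failing mesalazine are being enrolled. The documents do not say so: no criterion requires active disease or inadequate response, and a current user may be in remission with fatigue (section 1 reports fatigue in 40.0% of Chinese patients in remission). The endoscopy criterion ("Underwent enteroscopy within the past 1 year") says nothing about medication.

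A reader might also infer that the 71% rate applies only to new starters. The source population is not described, so this cannot be shown. One can assume 20-50% response among prior users and compute 0.71(1-f) + r·f, which gives a pooled control rate of 35-65%. That rests on two guesses and concerns an effective rate, whereas the primary outcome is a score. Even for the rate, the direction of any power change depends on what is held constant. With 56 per arm, 25-75% prior users and 30-50% response among them, one-sided power moves from 95% to 80-91% if the absolute gain is kept, but to 97-99.7% if the odds ratio is kept.

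Two printed facts survive: the eligibility list omits the one drug common to both arms, and the stated test for means is unadjusted.

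**Conclusion.** The point holds as a design and interpretation weakness. It is not an error of validity. Prior mesalazine use is left open at entry, and the stated comparison does not use it. The pooled IBD-F difference is therefore an unlabelled average over two contrasts, and before/after stool change mixes starting mesalazine with continuing it.

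The size is modest and rests on assumptions, because the documents give neither the share of prior users nor their outcome. Chance imbalance has a 95% limit of about 15-17 points (30-70% prior users, 70 per arm). Adjustment would remove about 2-14% of residual variance (shift of 0.3-0.8 SD, 50% prior users). Loss of power on the primary outcome cannot be computed from the documents. The applicability of the 71% rate to a mixed population is unsupported rather than shown to be wrong.

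**What to change.** 1. State in the eligibility section how prior and current mesalazine use is handled, so that sites read exclusion 3 the same way.
2. Record mesalazine/5-ASA use in the 4 weeks before entry (yes/no, the window exclusion 3 already uses) at the week -1 medical history.
3. Use it as a randomisation stratum and keep it in the analysis. Recruitment was planned from January 2024, so if allocation has begun, make it a prespecified covariate in the week 12 IBD-F and stool comparisons, in place of the unadjusted test.
4. Report differences by prior use descriptively only, given about 28 evaluable per arm per stratum at 50% prevalence.
5. Interpret before/after stool change as including the start of mesalazine only in non-users.
6. State which patients the 71% rate describes.

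The cost is one data field and one extra stratification factor or model term, with no added patients or visits. The downside is one more factor in allocation and stratum estimates that will be imprecise.
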